## Abstract

**Introduction:** Once-weekly or once-monthly injectable depot buprenorphine is a new opioid substitution treatment (OST) medication that provides clinically relevant plasma concentrations without daily peaks. Together with a high tolerability and acceptance reported by patients, the prolonged release of injectable depot buprenorphine might have beneficial implications on the patients' quality of life and social participation. The primary objective of this prospective non-interventional observational study is to evaluate the effects of subcutaneous injectable depot buprenorphine on the quality of life of patients in routine OST care in Germany. Secondary outcomes like illicit substance use, psychological distress, social participation and activity are assessed to provide an overall evaluation toward addiction recovery.

**Methods and Analysis:** The present study is a non-randomized prospective observational study with a control group (treatment-as-usual). To ensure comparability between both patient groups, suitable control patients (*n* = 213) from the same OST unit will be matched pairwise to each patient treated with injectable depot buprenorphine (*n* = 213). Matching variables are gender, duration of OST, take-home prescription and psychosocial functioning (according to the Global Assessment of Functioning scale). Primary study endpoint is the difference of change in quality of life, assessed with the recently developed Opioid Substitution Treatment Quality of Life scale (OSTQOL), within the depot buprenorphine group between baseline and month 12. The primary analysis will be carried out according to the intention-to-treat principle (ITT) by comparing OSTQOL mean scores using dependent *t*-tests. For secondary analyses, group comparisons will be done by mixed model approaches with baseline OSTQOL score and the (pairwise) cluster term as covariates.

**Discussion:** The study combines clinical, routine OST care data with relevant patient reported outcome data. The pairwise matching allows conclusions on effects of different OST medications. The study findings will provide new insights in the addiction recovery processes of OST patients treated with depot buprenorphine.

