### Secondary Outcome Measures

Secondary endpoints include the difference in the OSTQOL score between depot and control group at month 12 (t_4_), comparisons between the depot and control group in patient satisfaction (Client Satisfaction Questionnaire–CSQ-8) at month 12 (t_4_), substance use (i.e., on the basis of self-reporting) at month 6 (t_3_) and month 12 (t_4_), the retention rate in treatment at month 12 (t_4_), psychological distress (Brief Symptom Inventory 18) at t_4_, social participation at month 6 (t_3_) and month 12 (t_4_) as well as the cost-effectiveness (on the basis of quality-adjusted life years (QALYs); EuroQOL five dimensions questionnaire (EQ-5D) at month 12 (t_4_). Three secondary endpoints will be measured solely in the depot group, the acceptance of the depot medication and its application measured by the Treatment Satisfaction Questionnaire for Medication (TSQM-14) at month 1, 3, 6 and 12 (t_1_-t_4_), the dosage adequacy measured by the Opiate Dosage Adequacy Scale (ODAS) at month 1, 3, 6 and 12 (t_1_-t_4_) and changes in quality of life domains (OSTQOL subscales) in depot group over time between baseline (t_0_) and month 12 (t_4_). Possible adverse reactions will be assessed by a physician and recorded as part of the documentation of adverse events (AEs) and adverse drug reactions (ADRs). An overview of all primary and secondary outcome measures is provided in Table 1.

**Table 1 T1:** Overview of primary and secondary outcome measures.

**Primary outcome measure**	**Difference of OSTQOL total score in depot group between baseline (t_0_) and month 12 (t_4_)**
**Secondary outcome measures**	1. Quality of life (OSTQOL score) between depot and control group at t_4_ 2. Acceptance (TSQM-14) of injectable depot buprenorphine between t_1_ and t_4_ 3. Patient satisfaction with OST care (CSQ-8) between depot and control group at t_1_- t_4_ 4. Dosage adequacy (ODAS) in depot group at t_1_-t_4_ 5. Substance use (i.e., self-reporting) between depot and control group at t_3_ and t_4_ 6. Psychological distress (BSI-18) between depot and control group at t_4_ 7. Social participation between depot and control group at t_4_ 8. Retention rate (percentage of patients) in depot group at t_3_ and t_4_ 9. Cost-effectiveness [on the basis of quality-adjusted life years (QALYs); EQ-5D] between depot and control group at t_4_ 10. Changes in quality of life domains (OSTQOL subscales) in depot group between baseline (t_0_) and month 12 (t_4_)

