### Variables

The following variables will be collected at baseline (t_0_) and follow-ups [month 1 (t_1_), 3 (t_2_), 6 (t_3_), 12 (t_4_)]:

- **Sociodemographic data** including gender, age, current housing, work, family status/partnership.- **Health data** will be collected using the Opiate Treatment Index-Health Symptom Scale (OTI-HSS), a symptom checklist to assess the patient's current health status with regard to medical problems that opioid users often develop (e.g., injection-related problems, cardio/respiratory problems, musculoskeletal problems, neurological problems, gastro-intestinal problems (21, 22).- **OST data** (medication, doses) routinely collected by the OST practice/clinic.- **Quality of life** will be measured by the OSTQOL, a disease-specific instrument for measuring quality of life among patients in OST (20). First analyses in developmental processes of the OSTQOL showed acceptable internal consistencies of all subscales (personal development, psychological stress, social contacts, material well-being, OST and discrimination), with Cronbach's alpha between 0.75 and 0.88, as well as a good convergent and discriminant validity of the instrument (20).- The **patient acceptance** of injectable depot buprenorphine will be measured along the four key dimensions of the Treatment Satisfaction Questionnaire for Medication (TSQM-14) (effectiveness; side effects; convenience and global satisfaction).- The **Client Satisfaction Questionnaire (CSQ-8)** will be used to measure the patients' satisfaction with the overall OST care. The short 8-item instrument has been frequently used in substance use research including OST (23, 24) and has shown a high internal consistency and concurrent validity (25).- Parts (heroin craving, acceptance of the OST medication) of the **Opiate Dosage Adequacy Scale (ODAS)** will be used to measure the adequacy of opioid doses among the patients in the depot buprenorphine group. The ODAS consists of six domains (heroin consumption, narcotic blockade, mental and somatic opiate withdrawal syndrome, craving for heroin, and OST overdosing) including items which can be answered by the patient. Scores range between 1 (worst) and 5 (best). Cut-off scores of 3 or less in any ODAS domain will be regarded as not adequately dosed. The ODAS was found to have a good validity and reliability to measure and assess buprenorphine dose adequacy in the context of OST (26).- Data on **substance use** will be collected on the basis of patient self-report using the drug and alcohol use domain of the European Addiction Severity Index (EuropASI) (27). The data on substance use will be complemented by urine samples collected within routine OST care. The urine samples will be tested for heroin, non-prescribed substitutes, cocaine/crack, amphetamine, cannabis and benzodiazepine use.- **The psychological distress** among the patients will be measured by the Brief-Symptom-Inventory 18 (BSI-18), (28). The questionnaire comprises 18 items on physical and psychological symptoms, rated on a 5-point Likert scale (0 = not at all; 4 = very much) with regard to the last 7 days, and yields 3 sub-scores for depression, anxiety, and somatization, as well as an overall Global Severity Index (GSI).- **Social participation** will be measured by a self-developed short questionnaire including questions on the number and kind of social activities (e.g., recreational or physical activities, activities with friends, family) within the last week.- Data to calculate the **retention in treatment** will be collected by the date of ending OST or changing OST medication. The dates will be collected retrospectively by the treatment staff at any follow-up timepoint of the study. Retention in treatment will be calculated by dividing the number of patients in each study arm at each follow-up visit by the total number of patients in each study arm at baseline.- Quality-adjusted life years (QALYs) will be used for the **cost-effectiveness analysis**. Respective data will be collected with the EuroQOL five dimensions questionnaire (EQ-5D) (29).

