#### Secondary Outcome Analyses

Secondary data analyses will be carried out in accordance with the scale levels of the variables or scores and indices (drug consumption, somatic or mental health symptoms, quality of life, withdrawal symptoms, craving, treatment satisfaction) and along the expected relationships between individual variables, e.g., in the context of bivariate or multivariate analyses. Comparisons between depot patients and matched control group will be done by a mixed model approach with baseline OSTQOL score and the (pairwise) cluster term as covariates and will include all follow-up measurement points, such as month 3 and month 6 (see Table 2). Retention rates will be analyzed using descriptive statistics. For group comparisons, Chi^2^-tests (percentages) as well as Kaplan-Meier survival methods and Log-Rank Tests will be used. The significance level will be defined at *p* < 5%.

**Table 2 T2:** Overview of outcome domains, instruments and measurement.

**Outcome domain**	**Instrument**	**t_**0**_**	**t_**1**_**	**t_**2**_**	**t_**3**_**	**t_**4**_**
Quality of life	OSTQOL	x		x	x	x
Acceptance	TSQM-14	x	x	x	x	x
Patient satisfaction with	CSQ-8	x	x	x	x	x
OST care						
Dosage adequacy	ODAS	x	x	x	x	x
Substance use	EuropASI, Urine samples	x	x	x	x	x
Psychological distress	BSI-18	x			x	x
Social participation	Self-constructed questionnaire	x			x	x
Retention	CRF		x	x	x	x
Cost-effectiveness	EQ-5D	x			x	x
Health	OTI-HSS	x			x	x
Adverse events	AE, SAE, ADR	If necessary				

*t_0_, baseline; t_1_, month 1; t_2_, month 3, t_3_, month 6 and t_4_, month 12; OSTQOL, Opioid Substitution Treatment Quality of Life scale; TSQM-14, Treatment Satisfaction Questionnaire for Medication; CSQ-8, Client Satisfaction Questionnaire; ODAS, Opiate Dosage Adequacy Scale; EuropASI, European Addiction Severity Index; BSI-18, Brief Symptom Inventory 18; CRF = Case-Report Form; EQ-5D, EuroQOL five dimensions questionnaire; OTI-HSS, Opiate Treatment Index-Health Symptom Scale; AE, adverse event; SAE, serious adverse event; ADR, adverse drug reaction*.

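### The depot-versus-control mixed model names baseline OSTQOL as its only baseline covariate, so CSQ-8, BSI-18, substance use and social participation are not adjusted for their own t0 values

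*Protocol article*

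**What the plan says.** The Secondary Outcome Analyses section first lists several kinds of secondary variable, among them drug consumption, somatic and mental health symptoms, quality of life, craving and treatment satisfaction. It then gives one model for comparing the arms: "Comparisons between depot patients and matched control group will be done by a mixed model approach with baseline OSTQOL score". The only other covariate named there is a term for the matched pair; all follow-up visits are used, with a pointer to Table 2. The Abstract is at least as general: "For secondary analyses, group comparisons will be done by mixed model approaches with baseline OSTQOL score and the (pairwise) cluster term as covariates".

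The Secondary Outcome Measures section lists several comparisons between the arms besides OSTQOL. Examples are "comparisons between the depot and control group in patient satisfaction (Client Satisfaction Questionnaire–CSQ-8) at month 12" and "psychological distress (Brief Symptom Inventory 18) at t_4"; substance use, social participation and EQ-5D-based cost-effectiveness are also listed. Table 2 marks t0 for CSQ-8, EuropASI and urine samples, BSI-18, social participation and EQ-5D. No section says that any of these is adjusted for its own t0 value.

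Some secondary endpoints lie outside this model. Retention has its own methods: Chi² tests, "as well as Kaplan-Meier survival methods and Log-Rank Tests will be used". TSQM-14, ODAS and the OSTQOL subscales are depot-only and involve no group comparison.

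**The concern.** Patients choose their treatment. Under Study Design, controls are patients who do not want to switch to depot. The Treatment section suggests that patients with problems on their previous medication may be the more willing to take depot. The Discussion names the lack of randomisation as the main limitation. The arms may therefore differ at t0 in satisfaction, distress or substance use.

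Matching is on gender, duration of OST, take-home prescription and GAF percentile. None of these is the baseline of an affected outcome. Another scale's baseline removes only the part of a starting difference that it shares with the outcome. The remainder carries through to month 12 and can look like a medication effect in either direction. If the outcome's own baseline is the better predictor, leaving it out also widens the confidence interval.

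**Working it through.** **1. The plan's own figures.** A two-sided paired t-test with d = 0.25, α = 0.05 and power 0.80 needs 128 patients (noncentral t, power 0.8015). For drop-out, 128/(1 − 0.40) = 213.3, stated as 213. The detectable difference between the arms with 128 completers each is (1.960 + 0.842) × √(2/128) = 2.802 × 0.125 = 0.350, stated as 0.35. All three reproduce. None uses a covariate, so this point does not touch them.

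**2. Affected outcomes.**

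| Group comparison | Own t0 value in Table 2 | Baseline in the stated model |
|---|---|---|
| OSTQOL | yes | its own |
| CSQ-8, BSI-18, EuropASI use, social participation | yes | OSTQOL |
| EQ-5D / QALY | yes | OSTQOL, if this model is used; not stated |
| Retention | not applicable | not in this model |

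**3. Bias.** Let r be the correlation of the outcome's t0 value with its month-12 value, c the correlation of that t0 value with baseline OSTQOL, D the imbalance in the outcome's t0 value and D_Q the imbalance in OSTQOL (both in SD). Suppose OSTQOL acts on the month-12 outcome only through the outcome's t0 value. Adjusting for OSTQOL alone then leaves

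bias = r × (D − c × D_Q), with SE = √[(2/128) × (1 − (c·r)²)].

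The values of r, c, D and D_Q are assumptions. Central case: r = 0.6, c = 0.5, D = 0.2.

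- SE = 0.125 × √(1 − 0.30²) = 0.119.
- OSTQOL balanced (D_Q = 0): bias = 0.6 × 0.2 = 0.12 SD.
- OSTQOL imbalanced in proportion (D_Q = c × D = 0.10): bias = 0.6 × (0.2 − 0.05) = 0.09 SD.

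Results at D = 0.2, with the rejection rate of a nominal 5% test when there is no medication effect:

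| r | c | Bias, OSTQOL balanced | Rejects | Bias, OSTQOL imbalanced by c×D | Rejects |
|---|---|---|---|---|---|
| 0.5 | 0.3 | 0.100 | 12.8% | 0.091 | 11.4% |
| 0.5 | 0.7 | 0.100 | 13.7% | 0.051 | 7.2% |
| 0.6 | 0.5 | 0.120 | 17.2% | 0.090 | 11.7% |
| 0.7 | 0.3 | 0.140 | 20.9% | 0.127 | 18.1% |
| 0.7 | 0.7 | 0.140 | 25.0% | 0.071 | 10.0% |

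Against the planned detectable d of 0.35, a bias of 0.10 to 0.14 is 29% to 40% (0.10/0.35 and 0.14/0.35), and 0.09 is 26%. In this simplified model, adjusting for the outcome's own baseline removes this component.

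**4. Precision.** With r_Q the correlation of baseline OSTQOL with the month-12 outcome, the ratio of residual variances is (1 − r_Q²)/(1 − r²).

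- r = 0.5, r_Q = 0.4: 0.84/0.75 = 1.12.
- r = 0.6, r_Q = 0.3: 0.91/0.64 = 1.42.
- r = 0.7, r_Q = 0.2: 0.96/0.51 = 1.88.
- r = 0.5, r_Q = 0.5: 0.75/0.75 = 1.00, no loss.

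Over r = 0.5 to 0.7 and r_Q = 0.2 to 0.4, the detectable d is 0.32 to 0.34 with OSTQOL alone and 0.25 to 0.30 with the own baseline.

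**5. Simplifications.** The arithmetic treats a continuous outcome at month 12 with independent arms. It leaves out the pair term, the matching and the repeated visits, so it shows scale and does not predict this study's result.

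**The case against.** The strongest reply is that the sentence was written for the OSTQOL comparison. It mentions months 3 and 6, and in Table 2 only OSTQOL is followed at exactly months 3, 6 and 12. CSQ-8 and EuropASI also have month 1; BSI-18, EQ-5D and social participation have no month 3. On that reading baseline OSTQOL is the right covariate, and an article may leave the covariates for other outcomes to a fuller document. The same section also says that analyses follow the scale level of each variable.

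This is plausible and lowers confidence, but it does not settle the matter. The two months are given as examples, the pointer is to the whole of Table 2, and the Abstract speaks of secondary analyses in general. Scale level governs the type of analysis, not which baseline enters it. A plan that followed the printed text would carry the wrong covariate forward.

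The objection does rule out several stronger readings that a reader might infer:

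- *Every secondary outcome is misadjusted.* OSTQOL has its own baseline, and retention and the depot-only endpoints fall outside the model.
- *Baseline differences go uncorrected.* Pairs come from the same OST unit and are matched on GAF among other variables. OSTQOL has subscales on psychological stress, social contacts and OST that overlap in content with the affected outcomes. Part of any imbalance is therefore removed.
- *The QALY comparison is certainly affected.* No section places QALYs in this mixed model.
- *The test is known to be inflated to a given level.* The larger figures hold OSTQOL balanced, so that OSTQOL adjustment can remove nothing.

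**Conclusion.** The point holds for CSQ-8, BSI-18, EuropASI substance use and social participation, and for EQ-5D utility only if it is compared with this model. As printed, these are adjusted for baseline OSTQOL while their own t0 values go unused. The correction of baseline differences is then incomplete, and precision may be lost.

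The size rests on assumed values. For a 0.2 SD imbalance the residual bias is about 0.10 to 0.14 SD with OSTQOL balanced and about 0.09 SD in the central case with proportional imbalance. The precision loss ranges from none to nearly a doubling of the residual variance. Own-baseline adjustment does not remove other confounding, which remains possible in this design.

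This is a worthwhile improvement to secondary analyses, not a flaw that threatens the main result. The primary endpoint is a change within the depot group and does not use this model.

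**What to change.** In Secondary Outcome Analyses and in the Abstract, replace the baseline OSTQOL covariate by the baseline (t0) value of the outcome analysed (for OSTQOL, baseline OSTQOL), and keep the pair term. In practice this means t0 BSI-18 for distress, t0 CSQ-8 for satisfaction, t0 EuropASI use for substance use and the t0 questionnaire value for social participation. Baseline OSTQOL may stay as an optional additional covariate. State how the QALY comparison is analysed and adjust it for baseline EQ-5D utility.

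The cost is one sentence in each of the two places, plus a line on QALYs. No visits, data or patients are added, because Table 2 already schedules every t0 value needed.

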A pharmacokinetic evaluation shows clinically relevant plasma concentrations of buprenorphine without daily peaks, which suggests potential benefits of injectable depot buprenorphine in the avoidance of withdrawal symptoms (17). Accordingly, patients reported higher acceptability of injectable depot buprenorphine compared with the sublingual formulation (17). The long-acting formulation together with pharmacokinetic profiles and the high tolerability and acceptance reported by patients indicate that injectable depot buprenorphine can have beneficial implications on the patients' adherence as well as quality of life (17).

Previous literature compared changes in quality of life between depot buprenorphine and placebo (18, 19). Compared with placebo, patients receiving extended-release injectable buprenorphine showed significantly improved patient-reported outcomes with regard to health and medication satisfaction after 6 months (18). Moreover, their employment rate after 6 months increased, whereas the number of hospital days per person-year decreased (18). The 12-month follow-up confirmed that OST with subcutaneous injected buprenorphine can result in high retention and abstinence rates as well as in improved social aspects like employment (19).

In contrast to previous literature, this study will take a more naturalistic approach, by comparing not only against placebo, but against treatment as usual (TAU), which includes all registered OST medications, such as methadone or levomethadone, sublingual buprenorphine or slow-release oral morphine. By comparing against other forms of OST, including sublingual buprenorphine, we aim to evaluate the potential advantages that are specifically related to the depot formulation, e.g., the decrease of doctor-patient contacts, which might support patients' independence and social participation. In addition to generic quality of life and mental health instruments, we will use the new Opioid Substitution Treatment Quality of Life scale (OSTQOL) (20) as our main outcome measure, to account for the whole range of aspects of recovery that are relevant for opioid-dependent patients (20).

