### Treatment

The depot arm of the study will include opioid-dependent patients who are willing to switch or to initiate OST with one of two injectable depot buprenorphine formulations (once weekly or once monthly). Thus, this includes newly admitted patients who are starting with OST, as well as patients who are already in treatment (e.g., with racemic methadone, levomethadone, sublingual buprenorphine, slow release oral morphine). The participation in the study is voluntary and non-participation will not incur disadvantages neither for the physician (or the OST unit) nor for the patient. In this respect, there will be no increased risk resulting from study participation. Patients who were facing problems with their previous OST medication might benefit from study participation, and probably show an increased acceptance and willingness to use subcutaneous, injectable depot buprenorphine. Further, OST providers might benefit from expanded, more individualized therapeutic options for OST patients. Based on the clinical experiences gained so far, injectable depot buprenorphine is highly accepted by patients, and its side effect profile is comparable to sublingual buprenorphine with few, mild and reversible injection site reactions (17).

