### Assessment and Timelines

All data will be collected in case-report-forms (CRFs) including documentation sheets for clinical routine data and questionnaires for OST providers and patients. After baseline (t_0_), follow-up assessments will be made on month 1 (t_1_), month 3 (t_2_), month 6 (t_3_), and month 12 (t_4_). For the case that OST ends prematurely (before the end of the 12-month study period), study participation continues, and the patient will be asked to take part in the remaining follow-up assessments. All patients will receive reimbursements of € 10,-for each assessment.

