#### Safety Analysis

Adverse events (AEs) will be documented by medical OST staff. An AE is defined as any new untoward medical occurrence or worsening of a pre-existing medical condition in a clinical investigation subject administered study drug and that does not necessarily have a causal relationship with this treatment. An AE can therefore be any unfavorable and unintended sign (such as an abnormal laboratory finding), symptom, or disease temporally associated with the use of study drug, whether or not considered related to the study drug. The causal relationship to study drug is determined by a physician and should be used to assess all AEs.

A serious AE (e.g., life-threatening overdose) or possible other adverse drug reactions will be documented in the “Report on adverse drug reactions (ADRs)”. Analyses of safety outcomes will equally be conducted for both samples (PP and ITT).

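### Adverse events are the only domain in Table 2 without fixed visits, so their ascertainment may differ by arm, formulation and treatment status, in an unknown direction

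*Protocol article*

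**What the plan says.** Table 2, under Secondary Outcome Analyses, gives the schedule for t0 (baseline) to t4 (month 12). Its last row reads "AE, SAE, ADR If necessary"; all other rows carry marks at named visits, including retention, which is a CRF item.

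On method, the Safety Analysis section states: "Adverse events (AEs) will be documented by medical OST staff". Secondary Outcome Measures adds that a physician assesses possible adverse reactions. Handling With AEs and ADRs describes an event sheet that records, among other things, intensity and frequency, a 24-hour route to study management for serious events, and reporting of all events in the final report. None of these sections gives a standard question or a visit at which it is put.

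On contact, the Introduction lists as an example of a potential depot-specific advantage "the decrease of doctor-patient contacts, which might support patients' independence and social participation". The Treatment section allows a weekly or a monthly formulation.

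On follow-up, Assessment and Timelines says that if OST ends early, "study participation continues, and the patient will be asked to take part in the remaining follow-up assessments". Selection and Treatment of Participants says the same for patients who stop depot.

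**The concern.** The Safety Analysis section defines an adverse event broadly: any new or worsened medical occurrence, related or not. Counts under so broad a definition depend heavily on whether and how often patients are asked. If recording is driven by events that come to staff attention, the count reflects tolerability and opportunity for detection together. Opportunity may vary with the treatment under study, with the injection interval, and with whether the patient is still in OST.

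At stake are the adverse event and ADR frequencies in the final report. Readers will set depot beside usual treatment, or weekly beside monthly, whether or not a test is run. The primary endpoint, the change in OSTQOL within the depot group, is not affected.

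**Working it through.** The article states no adverse event rate, duration, detection probability or contact frequency, so there is no figure to reproduce. The check compares sections and then illustrates the mechanism under labelled assumptions.

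**1. Scheduled prompts that could bring an event to light** (Table 2, Variables, Secondary Outcome Measures)

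| Item | Visits | Arm | What it captures |
|---|---|---|---|
| AE, SAE, ADR | none fixed | not stated | any new or worsened event |
| OTI-HSS | t0, t3, t4 | both | current symptoms |
| TSQM-14, side-effects dimension | t1 to t4 as an endpoint | depot only | side effects of the medication |

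At months 1 and 3 the only scheduled item that touches side effects is an outcome in one arm. The OTI-HSS is common to both arms, but it is absent at those visits, asks about current status, and is not adverse event reporting. An event that has resolved before month 6 or month 12 would not show in it.

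**2. Direction**

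- Fewer contacts on depot, if they occur, would lower recording there, more so with monthly than weekly injections.
- The depot-only TSQM-14, and staff alertness to a new product, would raise it.
- A patient who has left OST may have no routine contact with the recording staff between study visits, in either arm.

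These act in different directions and none is quantified, so the net sign is unknown.

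**3. Illustration of the contact mechanism.** Assume an event lasting D days is recorded only if a contact falls within it, contacts are I days apart, and there is no recall. Then detection = min(1, D/I).

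- D = 7: I = 28 gives 7/28 = 0.25; I = 7 gives 7/7 = 1.
- D = 3: I = 28 gives 3/28 = 0.11; I = 7 gives 3/7 = 0.43; I = 1 gives 1.

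With full recall at the next contact every value becomes 1 and the difference vanishes. Daily contact also does not describe control patients with take-home prescriptions.

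**4. Effect on a descriptive ratio.** Assume a true risk of 20% in both arms; observed risk = 0.20 × detection.

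- Control detection 90%: 0.20 × 0.90 = 18%.
- Depot detection 70%, 50%, 30%: 14%, 10%, 6%; apparent ratios 14/18 = 0.78, 10/18 = 0.56, 6/18 = 0.33.
- Reversed, depot 90% and control 70%: 18/14 = 1.29.
- Equal detection: ratio 1.

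All detection values here are assumptions.

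**5. A related point of definition.** The Safety Analysis definition refers to an event "in a clinical investigation subject administered study drug", whereas Handling With AEs and ADRs records the causal link to the substitution medication. The Safety Analysis definition leaves it unclear whether events in control patients count. Yet safety is to be analysed in the ITT sample, whose definition in Primary Outcome Analysis covers both arms.

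**The case against.** The strongest reply is that the entry in Table 2 may mean only that the event sheet is filled in when an event has occurred, possibly at the common visits, and that the wording of any question belongs in the CRF or full protocol, which a journal article condenses. This stands in part: the article does not say that patients are not asked, and a reader who infers that nothing prompts an adverse event question at the visits goes beyond the text. What remains is that the article does print a schedule, and adverse events are the one domain it leaves without a visit.

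Several further points also stand:

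- Fewer contacts are presented as a potential advantage, not a fact. Matching on take-home prescription means that some controls may also attend infrequently.
- Both arms share the same visits. According to Data Processing, Missing Data, the OST unit carries out the follow-up, so patients off treatment who attend do meet the unit that records events. It is not shown that their events would be lost.
- Safety is neither a listed objective nor a Table 1 outcome, and no comparison by arm or formulation is announced. A reader might infer that a biased test is planned; the document does not support that.
- Event-driven recording by treating staff fits a non-interventional study.

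These points limit the strength of the claim. They do not supply a uniform prompt.

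**Conclusion.** The point holds as a risk, not as a demonstrated bias. The printed schedule fixes no visit for adverse events, and the article's other features make ascertainment plausibly dependent on arm, formulation and treatment status. It is tempting to conclude that detection will differ and will favour depot. The article does not support that: contact frequencies are not given, the OTI-HSS softens the problem, and the depot-only side-effects questionnaire pulls the other way.

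The size cannot be computed from the article. The detection values of 0.25 and 0.11 assume no recall and a 28-day contact interval; they show how the mechanism works and estimate nothing. The consequence is confined to the descriptive adverse event frequencies in the final report. The conclusion assumes that the schedule as printed is the schedule in use, and it takes the two sections that keep patients in follow-up after they leave depot or OST at their word. The Drop-Outs section can be read as ending follow-up at OST termination for patients who change groups, and should be reconciled with them.

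**What to change.** In Table 2, replace the present entry with an x at t1, t2, t3 and t4 for both arms. At each of these visits put one identical standard question: any new or worsened health problem, overdose or hospital stay since the last assessment, with onset and end dates and the OST medication at the time. Ask it also of patients who have left depot or OST, and state that events in control patients count. Keep event-driven reporting, including the 24-hour route, for SAEs and ADRs. Report events found at scheduled visits separately from those reported between visits, and base any comparison by arm or formulation on the former.

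The cost is one item on follow-up forms that OST staff already complete at every timepoint, with no added visit or staff. The downsides are more mild events on record and some recall error over the longer intervals (three months from t2 to t3, six from t3 to t4). Because recruitment began in April 2020, visits completed before the change would lack the item and should be identified as such. If the full protocol or CRF already contains such a question, correcting the Table 2 entry is enough for collection; the separate reporting would still need to be stated.
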